## Materials and methods

### Trial design

The Interactive Malaysian Childhood Healthy Lifestyle (*i-MaCHeL*) study is a single-blind, two-group cluster randomised controlled trial that evaluates the efficacy of a 3-month weight-related behaviours intervention in preschool child-parent dyads. The child-parent dyads will be randomised at the preschool level into either the intervention or control group at a 1:1 ratio. The present study protocol has been described according to the Standard Protocol Items: Recommendations for Interventional Trials (SPIRIT) 2013 statement [27, 28]. [Note: Completed SPIRIT checklist (S1 checklist) and TIDieR checklist (S2 checklist) were submitted along with the manuscript to the journal].

### Study setting

The present study will be conducted in the state of Terengganu, located on the East Coast of Peninsular Malaysia. There are eight districts of Terengganu, and this study will only include two districts: Kuala Terengganu and Kuala Nerus. These two districts are chosen based on demographic and logistic factors as they are within the study centre’s 35 miles (56 kilometres). Nevertheless, after careful consideration before selection, these two districts covered both urban and rural locations.

### Eligibility criteria

#### Eligibility (inclusion/exclusion criteria) of preschools

All preschools within Kuala Terengganu and Kuala Nerus districts will be eligible for inclusion. There are 71 preschools in the districts. Because of varying cluster size, the preschools with fewer than 26 children (minimum cluster size to be recruited) will be excluded from the study [10].

#### Eligibility (inclusion/exclusion criteria) of child-parent dyads

Within participating preschools, all children aged 5- and 6-year Malaysian citizens will be eligible for inclusion in the recruitment phase. The parent/guardian of the preschool children are eligible for the study if they could read and understand either English or Malay; are aged between 25 to 49 years; have regular internet access via a tablet device, mobile phone, or computer/laptop; have regular access to a phone with texting capability; have WhatsApp accounts or agree to create the accounts and; are comfortable to read/view materials on electronic devices. The age range of parents (with 5- or 6-year children) is between 25 to 49 years is applied in the present study to ensure that the parents are comfortable enroling in the fully online intervention.

Child-parent dyads will be excluded if the children are taking medications or have a medical condition with the potential to affect the weight or restrict age-appropriate play; the children have conditions that require the restriction of certain foods (e.g., celiac disease or food allergies) and; the parents suffer from a severe physical or psychological illness, making the study too demanding for the family.

### Sample size

The sample size is calculated for the primary outcome, BMI z-score. The sample size for individual randomisation of the present study is based on Formula 1 [29]. The values used in the sample size calculation are based on the BMI z-score data from Ahmad et al. (2018) [30] study, which is 1.95±0.45 and 2.09±0.35 for the treatment and control groups, respectively. Based on Formula 1, a calculated sample size required for each group arm is 131 child-parent dyads. It is calculated that, with at least 80% power to identify a small to medium effect size [31] at the 5% significance level, the present study needs a total of 262 child-parent dyads for the two-group arm.

$${}^{n}Individual\_Binary=\frac{{\left(z_{1-\frac{\alpha }{2}}+z_{1-\beta }\right)}^{2}[\sigma_{trt}^{2}+\frac{\sigma_{con}^{2}}{r}]}{\Delta^{2}}$$
(1)

**where**, $r=\frac{n_{con}}{\sigma_{con}},\Delta =\mu_{trt}-\mu_{con}$

*μ*_*trt*_ = Mean in treatment group = 1.95

*μ*_*con*_ = Mean in control group = 2.09

*σ*_*trt*_ = SD. in treatment group = 0.45

*σ*_*con*_ = SD. in control group = 0.35

*z* = Critical *z* value for a given Alpa (*α*) = 0.05 (two − sided) and Beta (*β*) = 0.2 with the value of $z_{1-\frac{\alpha }{2}}$ = 1.96 and *z*_1−*β*_ = 0.84

*r* = Ratio of the two sample sizes = 1/1

An adjustment using the design effect (DE) is made for the calculated sample size to allow for the design structure (due to the cluster sampling method), which results in larger sample sizes [32]. Taking into account unequal cluster size [10], assume the mean cluster size of 38 child-parent dyads will be recruited per preschool. Based on the Formula 2 [32, 33], given that the number of individuals per cluster (*n*) in the present study is 38 child-parent dyads and the Intra-cluster correlation coefficient (*ρ*) from the previous studies is 0.01 [18, 34], the calculated design effect of the present study is 1.37.

Designeffect(DE)=1+(n–1)ρ
(2)

By considering the design effect is 1.37 and the sample size required for each group arm (^*n*^Individual_Binary) is 131 (see Formula 3), the total sample size of the individual randomisation is further increased from 262 to 360 child-parent dyads.

$$({}^{n}Individual\_Binary)\times Design\;effect\times 2$$
(3)

After estimating a loss to follow-up of 20% for this trial, the final sample size is increased to a total of 460 child-parent dyads (230 per group arm). Thus, based on the total number of participants in the two groups is 460 and the number of individuals per cluster is 38 child-parent dyads (see Formula 4), a calculated number of preschool clusters in the present study is 12 preschools. Therefore, 6 preschool clusters will be randomised to each experimental and control group.

$$n\_cluster=\frac{Total\;number\;of\;participants\;in\;the\;two\;groups}{number\;of\;individuals\;per\;cluster}$$
(4)

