## Introduction

In recent years, the prevalence of unhealthy weight in children has been alarming in many countries. Overall, in World Health Organization European Region, 28.7% of boys and 26.5% of girls (aged 6 to 9 years) were overweight (including obese), and 2.5% and 1.9%, respectively, were thin (COSI 2015–2017) [1]. In Malaysia, overweight and obesity coexist with thinness among children and adolescents. The National Health and Morbidity Surveys (NHMS) previously carried out in 2019 reported that 29.8% of children and adolescents aged 5 to 17 years were classified as either overweight or obese, and another 10% were classified as thin [2]. Furthermore, a growing trend toward the prevalence of childhood obesity has also been seen in Malaysia over the last few decades. The National Health and Morbidity Surveys (NHMS), previously carried out in 2011 and 2015, showed that the prevalence of obesity among children aged 5 to 9 years was increased from 6.7% in 2011 [3] to 14.8% in 2015 [4]. Thus, unhealthy nutritional status, especially childhood obesity, is considered one of the most significant public health issues in Malaysia.

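### The stated 80% power for BMI z-score is not supported for the children enrolled: its SDs and 0.14 difference describe children near z = +2, but recruitment is open to all weights

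*Protocol article*

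**What the plan says.** Under Sample size, the protocol article states that "The sample size is calculated for the primary outcome, BMI z-score". The means and SDs come from one cited study: "which is 1.95±0.45 and 2.09±0.35 for the treatment and control groups, respectively". They enter Formula 1, a two-sample comparison of means with no term for baseline. The result is that "a calculated sample size required for each group arm is 131 child-parent dyads", and the claim is "with at least 80% power to identify a small to medium effect size [31] at the 5% significance level". The section then says "assume the mean cluster size of 38 child-parent dyads will be recruited per preschool", takes an intra-cluster correlation of 0.01 (design effect 1.37), reaches 360 dyads, and allows 20% loss to arrive at 460 dyads in 12 preschools.

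The eligibility section for child-parent dyads has no weight or BMI criterion: "all children aged 5- and 6-year Malaysian citizens will be eligible for inclusion in the recruitment phase". It does exclude children with medical conditions or medication that may affect weight. The Introduction describes the national background as "29.8% of children and adolescents aged 5 to 17 years were classified as either overweight or obese, and another 10% were classified as thin". Statistical methods plans subgroups by weight status, which presupposes mixed-weight enrolment, and says that the primary analysis adjusts for clustering and for the baseline value of the outcome.

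**The concern.** The planning inputs and the eligibility rule describe different children. A group with mean z near 2 and SD near 0.4 is almost entirely overweight and is narrow on the z scale. An intake of all weights is centred lower and is wider. Formula 1 depends on the square of the SD, so an SD that is too small for the enrolled population translates directly into power that is not there. The difference of 0.14 comes from the same source and is carried over without argument.

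At stake is how the primary result is read. If the trial finds no difference, the stated power sets how much weight that finding carries. As written, the figure rests on a population that the trial does not recruit.

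**Working it through.** **Inputs from Sample size:** means 1.95 and 2.09, SDs 0.45 and 0.35, two-sided 5%, 80% power (z = 1.96 and 0.84), cluster size 38, ICC 0.01, 20% loss, 6 preschools per arm.

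**1. Reproducing the plan.**
- Per arm: (1.96 + 0.84)² × (0.45² + 0.35²) / 0.14² = 7.84 × 0.325 / 0.0196 = 130.0 (130.1 with unrounded z, hence 131).
- Design effect: 1 + 37 × 0.01 = 1.37. Total: 131 × 1.37 × 2 = 358.9 (stated 360).
- Loss: 360 / 0.8 = 450 (stated 460).
- Average SD: √((0.45² + 0.35²)/2) = 0.403, so the standardised difference is 0.14 / 0.403 = 0.35.
- With 360/2 = 180 completers per arm, the effective number is 180 / 1.37 = 131.4 and √(2/131.4) = 0.1234. Power at SD 0.403 is 80.4%.

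The arithmetic is sound to within small rounding differences. The question is the inputs.

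**2. Do the inputs fit the enrolled children?** Under normality, the share below z = +1 is Φ((1 − 1.95)/0.45) = 1.7% in the treatment group and Φ((1 − 2.09)/0.35) = 0.1% in the control group. The Introduction's national figures leave about 70% neither overweight nor obese (ages 5 to 17).

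**3. An SD for unselected 5- and 6-year-olds.** The protocol gives none, so this is an assumption with a range. A z-score has SD about 1 in its reference population. Fitting a normal curve to the Introduction's prevalences, with assumed cut-offs of +1 and −2, gives:
- Malaysia, 29.8% and 10%: 3 / (0.530 + 1.282) = 1.66, mean about 0.12
- European boys aged 6 to 9, 28.7% and 2.5%: 1.19
- European girls aged 6 to 9, 26.5% and 1.9%: 1.11

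The value 1.66 is therefore an upper end that depends on which figures are used. The range taken is 0.8 to 1.66.

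**4. Unadjusted power for 0.14, as in Formula 1.** Power ≈ Φ(0.14/(SD × 0.1234) − 1.96), plus the negligible other tail. The detectable difference at 80% power is 2.80 × SD × 0.1234.

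| SD | Power for 0.14 | Detectable difference |
|---|---|---|
| 0.8 | 29% | 0.28 |
| 1.0 | 21% | 0.35 |
| 1.3 | 14% | 0.45 |
| 1.66 | 11% | 0.57 |

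Using 184 completers per arm (80% of 230) changes these by a point or less.

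**5. With the planned baseline adjustment.** Replace SD by SD × √(1 − r²), where r is the baseline-to-follow-up correlation. The protocol does not give r, so these values are assumed.

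| SD | r = 0.80 | r = 0.90 | r = 0.95 |
|---|---|---|---|
| 0.8 | 66% | 90% | >99% |
| 1.0 | 47% | 74% | 95% |
| 1.3 | 31% | 52% | 80% |
| 1.66 | 21% | 35% | 59% |

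The r at which the residual SD equals 0.403 is √(1 − 0.403²/SD²): 0.86 at SD 0.8, 0.92 at 1.0, 0.94 at 1.2, 0.95 at 1.3 and 0.97 at 1.66.

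**6. Few clusters.** The figures above use the normal approximation. With t on 10 degrees of freedom (12 preschools less 2), the plan's own 80% becomes 72%.

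**7. The target difference.** If the average difference were 0.07 instead of 0.14 (half, for illustration only), power at SD 1.0 and r = 0.95 would be about 44%.

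**The case against.** The strongest reply is that the primary analysis adjusts for baseline, so the SD that matters is the residual SD, not the spread between children. The planning SD of 0.403 is exactly the residual SD of a population with SD 1.0 and r = 0.915. With r = 0.95, the design has 95% power at SD 1.0 and about 80% at SD 1.3. This stands as far as it goes, and it rules out several stronger readings:

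- A reader might infer that 80% power is definitely absent. The protocol does not support that, because it gives neither r nor the SD, and a high enough r would restore the claim.
- A reader might infer that the planning SD is 2.5 to 4 times too small (1.0/0.403 to 1.66/0.403). That compares it with the unadjusted SD, and the upper end needs assumed cut-offs, normality and prevalences for ages 5 to 17.
- A reader might dilute the effect to 0.298 × 0.14 = 0.042, on the view that only overweight children respond. The protocol says nothing about effect by weight status, so this is at most an illustration.

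What the reply does not do is rescue the paragraph as written. Formula 1 contains no correlation, the SDs are not described as residual or change-score SDs, and the carry-over to an all-weight sample is not justified. Nor does baseline adjustment answer whether 0.14 is a sensible average difference for these children.

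It is also fair to say that allocation, type I error and the planned analysis are untouched.

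**Conclusion.** The point holds in this form: the claim of at least 80% power for a 0.14 difference is not supported for the population enrolled. On the protocol's own formula and design effect, power is about 29%, 21%, 14% and 11% at SDs of 0.8, 1.0, 1.3 and 1.66, and the difference detectable at SD 1.0 is about 0.35. Under the planned baseline-adjusted analysis, power at SD 1.0 runs from 47% to 95% as r goes from 0.80 to 0.95, and 80% needs about 0.92, before a correction for 12 clusters. The result rests on an assumed SD range, assumed correlations and the full 0.14 being kept. The mismatch between inputs and eligibility follows from the protocol's own text, with normality assumed for the share below +1. This should be fixed. It is an unsupported planning assumption with a conditional loss of power, not an error in the arithmetic or the analysis.

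**What to change.** Restate the Sample size paragraph for the children who will be enrolled:

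- Give an SD for unselected 5- and 6-year-olds, with its source.
- Use variance SD²(1 − r²), with a stated r, so that the calculation matches the baseline-adjusted primary analysis.
- Justify the target difference for an all-weight sample.
- State the difference detectable with 12 preschools and the planned completers, preferably with a small-sample correction for the number of clusters.
- Make the 80% claim explicitly conditional on SD, r and the target difference, or remove it.
- Check SD and r on pooled data without reference to arm.

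The cost is one rewritten paragraph and probably a less favourable stated power. No extra dyads or measurements are needed.

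### With 6 preschools per arm, the stated inputs give about 74–75% power for the comparison unadjusted for baseline, not at least 80%

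*Protocol article*

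**What the plan says.** The protocol article, under Sample size, sizes the trial on BMI z-score. The planning values come from an earlier study, "which is 1.95±0.45 and 2.09±0.35 for the treatment and control groups, respectively". Formula 1 uses z values of 1.96 and 0.84 and gives 131 dyads per arm, "with at least 80% power to identify a small to medium effect size" "at the 5% significance level". On cluster size the section says: "Taking into account unequal cluster size [10], assume the mean cluster size of 38 child-parent dyads will be recruited per preschool". Formula 2 is 1+(n–1)ρ; with n = 38 and ρ = 0.01 it gives 1.37. The total becomes 360, then 460 after 20% loss to follow-up, and dividing by 38 gives 12 preschools. "Therefore, 6 preschool clusters will be randomised to each experimental and control group".

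Two other sections bear on the point. Under Eligibility criteria, cluster sizes are said to vary, and preschools with fewer than 26 children are excluded. Under Statistical methods, the primary analysis is to be adjusted for clustering and for the baseline value of the outcome.

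**The concern.** Normal quantiles assume that the variance of the treatment contrast is known, or is estimated from many independent units. Here the independent units are 12 preschools. An analysis that respects the clustering estimates the between-preschool variance from 12 − 2 = 10 degrees of freedom and must use a critical value of 2.23 instead of 1.96. No step in the calculation allows for this, either by t quantiles or by added clusters.

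Formula 2 is also the equal-cluster form. Only the mean of 38 enters it, so the statement that unequal size has been taken into account does not match the formula that follows.

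Both omissions make the stated power too high. This is the power claim for the primary outcome, so a null result would be read against a figure that does not follow from its own inputs.

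**Working it through.** **Inputs, all from Sample size unless noted.** SDs 0.45 and 0.35; difference 2.09 − 1.95 = 0.14; two-sided α = 0.05; ICC 0.01; mean recruited cluster size 38; 20% loss; 6 preschools per arm; 1:1 allocation (Trial design). The documents give no CV of cluster size and no baseline correlation. Values used for these below are assumptions.

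**Step 1: reproduce the plan.**
- Variance sum: 0.45² + 0.35² = 0.325.
- Formula 1: (1.96 + 0.84)² × 0.325 / 0.14² = 130.0; with unrounded quantiles 130.15, rounded up to 131.
- Design effect (DE): 1 + 37 × 0.01 = 1.37. Total: 131 × 1.37 × 2 = 358.9 (stated 360).
- Loss: 360 / 0.8 = 450 (stated 460). Clusters: 460 / 38 = 12.1, so 12.

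The chain reproduces apart from upward rounding. Normal-quantile power at 360 dyads with DE 1.37 is 80.4%, so the stated 80% is what the printed formulas give.

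**Step 2: replace the normal quantile by t on 10 degrees of freedom.** The number analysed after 20% loss is 360 (the plan's target, 30 per preschool) to 460 × 0.8 = 368 (30.7 per preschool). The design effect is taken at the analysed cluster size.

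SE = √(0.325 × DE / n per arm); λ = 0.14 / SE; power from the noncentral t with 10 degrees of freedom and critical value 2.228.

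| Analysed | DE | SE | λ | Power, normal | Power, t(10) |
|---|---|---|---|---|---|
| 360 | 1.290 | 0.0483 | 2.90 | 82.7% | 74.4% |
| 368 | 1.297 | 0.0479 | 2.925 | 83.3% | 75.1% |

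The change of reference distribution alone costs about 8 points. On t(10), 80% power needs λ of about 3.11, so the detectable difference is 3.11 × 0.0479 = 0.149 at 368 analysed and 3.11 × 0.0483 = 0.150 at 360.

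**Step 3: add variation in cluster size (CV assumed).** DE = 1 + [(1 + CV²) × mean − 1] × ICC, at 368 analysed:

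| CV | DE | Power, t(10) | Simulated power, weighted cluster-mean t-test |
|---|---|---|---|
| 0 | 1.297 | 75.1% | 75.5% |
| 0.3 | 1.324 | 74.2% | 74.1% |
| 0.5 | 1.373 | 72.7% | 72.6% |

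Unequal sizes take off about 1 point at CV 0.3 and about 2.5 points at CV 0.5.

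**Step 4: what baseline adjustment could return (correlation r assumed).** Multiplying the variance by 1 − r², on t(10) with 368 analysed, and letting CV run from 0.5 to 0:
- r = 0.3: 77–79%
- r = 0.4: 80–82%
- r = 0.5: 84–86%

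**The case against.** The strongest reply is that the unadjusted comparison is not the planned one. Statistical methods has the primary analysis adjust for the baseline value, and Step 4 shows that an assumed correlation of about 0.4 is enough to bring power back to roughly 80%. This stands, and it limits the point. A reader might infer that the trial falls short of 80% even if every planning assumption is true. The documents do not support that, because the power of the adjusted analysis depends on a correlation they do not give. The reply does not rescue the stated figure, though: the calculation neither credits baseline adjustment nor states a correlation.

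A reader might also put the protocol's own figure at about 72%. Two routes lead there, and neither uses the plan's inputs consistently and alone. One keeps DE 1.37, which belongs to 38 per preschool, while analysing 360 dyads, which is 30 per preschool; this gives 71.8%. The other needs an assumed CV of 0.5. With a mean of 38, that is an SD of 19, while the exclusion of preschools with fewer than 26 children limits the lower tail. It would take a long right tail.

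With full retention (460 analysed), t(10) power is about 82% with equal clusters and 79% at CV 0.5. But the protocol plans for 20% loss, and power should be judged at that loss.

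**Conclusion.** The claim of at least 80% power does not follow from the stated inputs. At the planned 20% loss, the comparison unadjusted for baseline has 74.4–75.1% power for a difference of 0.14, a shortfall of about 5 points, and 80% power for a difference of about 0.15. This rests on the protocol's SDs, ICC and retention, equal cluster sizes, and a test on 10 degrees of freedom. Nearly all of the shortfall is due to the degrees of freedom. Unequal cluster size is the minor part, but there the text claims an allowance that the formula does not contain. With an assumed CV of 0.3–0.5, power is about 74–73%.

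The arithmetic is not at fault, since the printed chain reproduces; the approximation is unsuited to 12 clusters. The shortfall is moderate and the planned baseline adjustment may offset it, so this should be corrected but does not invalidate the design.

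**What to change.** In Sample size, restate power using t on 10 degrees of freedom and DE = 1 + [(1 + CV²) × mean − 1] × ICC, with the CV taken from the preschool rolls. For the comparison unadjusted for baseline this gives about 73–75% for a difference of 0.14, or 80% for about 0.15, depending on the CV found. The sentence on unequal cluster size would then describe what was done.

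If the sponsor relies on the planned baseline adjustment to keep 80%, say so, state the assumed baseline correlation with its source, and show the power with it. About 0.4 or more is needed.

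The cost is a slightly less favourable stated figure, or one further stated assumption. No preschools or dyads are added.

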### Recruitment

#### Preschool recruitment

A list of the 71 preschools in Kuala Terengganu and Kuala Nerus will be obtained from the Terengganu State Education Department (the data is also available online at https://www.data.gov.my). After the screening for inclusion, 34 out of 71 preschools with less than 26 children will be excluded from the study. A list of 37 preschools will be eligible to participate in the present study. All the 37 eligible preschools will be assigned with a unique identification number and randomly ordered by an independent researcher using a random number generator software (Research Randomizer version 4.0) [35] to generate a list of random numbers. The eligible preschools will then be sequentially invited by email and phone call to achieve the target recruitment of 12 preschools. If the preschool decline to participate, the next preschool on the list will be approached. The first 12 preschools that agree to participate in the intervention programme will be enrolled in the study.

#### Child-parent dyads recruitment

A list of children attending the included preschools will be obtained from the preschool teachers. All child-parent dyads in the preschools will be screened for eligibility criteria, and then consent to participate will be obtained from them. Teachers will distribute the information sheets and consent forms to preschool children to deliver to their parents. Information sheets and consent forms will have an explanation of the nature of the research, study components, and the requirements of the participants. Once consent forms are collected and eligible child-parent dyads are determined, the baseline data will be collected. After completing the baseline measurements, the child-parent dyads will finally be enrolled in the intervention programme. (see Fig 1 for study outline).

